### Randomisation

Eligible participants in the BiBBS cohort will be individually randomised 1:1 to the intervention (*n* = 120) or control group (*n* = 120), using blocked randomisation with stratification by child age (1 year or 2 years at the time of randomisation) and ethnicity (White British, South Asian, or other). The six allocation sequences (one for each stratum) will be generated using Stata/SE v17.0 (for Windows 64-bit x86-64) or later, using the user-written Stata command ralloc (Ryan, 1997).

We will draw a stratified random sample of 240 participants from all eligible participants in the BiBBS database, with sampling fractions (approximately) proportional to the distribution of the six randomisation strata in the eligible cohort population. The *n*_*i*_ sampled participants in stratum *i* will then be randomly sorted and matched against the first *n*_*i*_ allocations in the allocation sequence for stratum *i*.

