### Feasibility outcomes

We have based the feasibility outcome targets on data from two key sources. The first relates to a postnatal data collection sweep conducted as part of the main BiBBS cohort study. The second is information on rates of IY-T enrolment, participation and completion (where an ‘enrolee’ is referred and seen face to face in at least one pre-course contact, a ‘participant’ is someone who attends at least 1 week of the groups, and a ‘completer’ is someone who attends at least 8 of the 13 group-based sessions) reported by Barnardo’s and the Better Start Bradford Innovation Hub (see https://borninbradford.nhs.uk/what-we-do/improving-health/bsb-innovation-hub/) Table 1.

**Table 1 Tab1:** Target figures

Projected target figures	Rationale for target figures
120 randomised to intervention → 84 women are contactable]	80% of women were contactable for the BiBBS postnatal sweep, which takes place approximately 12 weeks after recruitment into BiBBS. We will contact women 1–3 years after recruitment into BiBBS, and so we have set our rate to be lower at 70%.
84 women contacted → 44 women consent to the referral → 22 women enrol	On average, the rate of conversion from referral to enrolee in IY-T is 52%. We therefore anticipate that 52% of randomised BiBBs participants will agree to be referred, and 50% of those referred will enrol into the programme.
22 enrolees → 20 enrolees go on to participate	On average, 89% of enrolees to IY-T are converted into participants. We have set a target of 90% of randomised enrolees to be converted into participants.
20 participants → 12 participants go on to complete	60% of participants go on to complete IY-T. We have set our rate to be 60%.

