**Table 2 Tab2:**
[figure not shown]

[figure not shown]
Feasibility objectives and outcomes

Table 1 summarises our target figures and how these were decided upon, and Table 2 summarises these targets and outlines how feasibility objectives will be assessed. In addition to the above, we also aim to assess contamination (any overlap between allocated control group, and non-randomised intervention group participants) and aim for this to occur in <5% of the sample. This is based on an estimate that <5% contamination has a negligible effect on the required sample size for a trial [33]. A RAG rating system has been applied to support the feasibility assessment of each objective: to be rated as green (achieved), amber (partly achieved) and red (not achieved). For an objective to be achieved and rated green, it must reach the percentage level specified above (e.g. 70% for contactable women, 50% for converting randomised participants into referrals). The levels at which we reach amber are equal to the green target, minus 20%. This is except for the rate for contamination (objective 1.2), where the rates are set on achieving less than 5% contamination.

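### The referral criterion is stated on two denominators, contacted and randomised women, and read literally the green level is one that the study's own projection would miss

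*Protocol article*

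**What the plan says.** All the relevant statements are in the protocol article, Methods.

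- **Randomisation.** Participants are "individually randomised 1:1 to the intervention (*n* = 120) or control group (*n* = 120".
- **Feasibility outcomes, Table 1, first row.** "120 randomised to intervention → 84 women are contactable", a rate of 70%.
- **Table 1, second row, target.** "84 women contacted → 44 women consent to the referral → 22 women enrol".
- **Table 1, second row, rationale.** The service's average conversion from referral to enrolee is given as 52%. The text then continues: "We therefore anticipate that 52% of randomised BiBBs participants will agree to be referred, and 50% of those referred will enrol into the programme".
- **Rating paragraph after Table 2.** To be green, an objective "it must reach the percentage level specified above (e.g. 70% for contactable women, 50% for converting randomised participants into referrals". For amber: "The levels at which we reach amber are equal to the green target, minus 20" per cent. The paragraph does not say whether this is percentage points or a proportion of the target. Contamination has its own rule.

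Table 2, which is meant to set out how each objective is assessed, is a figure that is not shown in the available text.

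**The concern.** The target count, its rationale and the rating rule all describe one step, agreement to be referred. The count is a share of the women contacted. The rationale and the rating rule name randomised participants. The rating rule also claims to restate a level already given, yet the only 50% in Table 1 belongs to a later step, referred to enrolled.

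The choice of denominator changes the rating at the result the study itself expects. The red, amber and green ratings are the stated aid to judging feasibility, and the Discussion makes a larger trial depend on that judgement. If the denominator is chosen after the counts are known, the criterion is no longer prespecified.

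A second point concerns the source of the 52%. It was observed for conversion from referral to enrolment, but it is used for the earlier step from contact to consent, for which the article gives no observed rate.

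**Working it through.** **Inputs.** 120 randomised to intervention (Randomisation section). 70% contactable, 52% agreeing to referral, 50% of those referred enrolling, 90% of enrolees participating and 60% of participants completing (Table 1). Green at 50% for referrals, and amber at green minus 20% (rating paragraph).

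**Step 1: reproduce the plan's own figures.**
- Contactable: 120 × 0.70 = 84.
- Consent to referral: 84 × 0.52 = 43.7, rounded to 44.
- Enrol: 44 × 0.50 = 22.
- Participate: 22 × 0.90 = 19.8, rounded to 20.
- Complete: 20 × 0.60 = 12.

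Every count in Table 1 is reproduced, and 44 arises only with contacted women as the base.

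**Step 2: apply the wording that names randomised participants.**
- Rationale: 120 × 0.52 = 62.4, not 44.
- Rating rule: 120 × 0.50 = 60, not 44.

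These two differ from each other by about two women. The gap that matters is between either of them and 44.

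**Step 3: rate a study that achieves exactly 44 referrals from 84 contacted, using the 50% in the rating paragraph.**

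| Denominator | Rate | Green needs | Amber floor, points | Amber floor, relative | Rating |
|---|---|---|---|---|---|
| 84 contacted | 44/84 = 52.4% | 42 women | not needed | not needed | Green |
| 120 randomised | 44/120 = 36.7% | 60 women | 50 − 20 = 30% (36 women) | 50 × 0.8 = 40% (48 women) | Amber if points, red if relative |

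**Step 4: how far the literal threshold is from the projection.** The 95% Wilson interval for 44/120 is 28.6% to 45.6%, which excludes 50%. If the true rate were 44/120 and women responded independently (binomial), the chance of at least 60 referrals in 120 would be about 0.2%. At the projected contact rate, 60 referrals need 60/84 = 71.4% of contacted women to consent, against the 52% projected. At 50% enrolment they would give 60 × 0.50 = 30 enrolees, against the 22 projected and the 24 places in two groups of 12.

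**Step 5: the borrowed rate.** Using the observed 52% at the step it describes gives 44 × 0.52 = 22.9, or 23 enrolees instead of 22. The effect on the counts is one woman.

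**The case against.** The strongest reply is that contacted women were meant all along. The second row of Table 1 starts from 84 contacted, so its percentage naturally applies to them. The article also uses the word randomised as a label for women who came through the trial. In the next row it says: "We have set a target of 90% of randomised enrolees to be converted into participants". That cannot be a share of 120, because the target is 20 of 22. The label has a purpose, since groups may be topped up with parents outside the study. On this reading the projection is 52.4% and green.

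This reply stands as a plausible account of intent. It does not make the text consistent, because the reader must still override the stated denominator in two places.

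Table 2 is unseen, and the 50% is given in the text only as an example. Table 2 may well state the denominator and settle the amber rule. It cannot make the visible target, rationale and rating sentence agree with one another.

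It is also fair that the ratings only support the assessment, that no automatic stop is attached to them, and that raw numbers, percentages and Wilson intervals will be reported. A reader could compute either ratio. That limits the harm but leaves the rating itself undefined.

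Finally, the 52% can be defended as a proxy for a step with no data. That is right: it is a weakly supported assumption and not an arithmetic error.

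**Conclusion.** The conflict is real and lies in the visible text. There are two denominators (contacted, randomised) and two percentages (52%, 50%), and the one that matters is the denominator: 44 referrals in Table 1, against 60 or 62 if the wording on randomised participants is taken at face value. At the projected result the referral criterion is green on contacted women. On randomised women it is amber or red, depending on how the 20% deduction is read.

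A reader might infer that a study on target is bound to miss green. The documents do not support that. It follows only from the literal wording of the rating paragraph, with Table 2 unseen and the word randomised used loosely elsewhere. Nor do they support an inference that the sample size or the Table 1 counts are wrong, since the whole sequence from 120 to 12 reproduces once contacted women are the base.

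The ratings above assume 120 randomised to intervention, 84 contacted and 44 consenting, as projected.

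**What to change.** 1. In Table 1 and the rating paragraph, define the referral criterion once, as women consenting to referral divided by women contacted, with a single green value of 52% (44 of 84) to match the projection.
2. In the Table 1 rationale and the rating sentence, replace randomised with contacted, and make Table 2 agree.
3. Say whether the 20% deduction for amber is in percentage points or relative. With green at 52%, the amber floor would be 52 − 20 = 32% (27 of 84) in points, or 52 × 0.8 = 41.6% (35 of 84) if relative.
4. State that the consent-to-referral rate is an assumption borrowed from the service's referral-to-enrolee rate.

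The cost is wording in Table 1, Table 2 and one paragraph. No participants, data collection or sample-size change is needed. Green at 52% asks for 44 of 84 contacted women, where 50% would ask for 42.

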### Trial management

The trial is considered low risk and oversight will be provided by the Incredible Years working group and the programme management group of the Innovation Hub. The study research team will be responsible for the allocation of participants to interventions, routine data linkage, and all data analysis. All other elements of the study will be performed by individuals external to the research team as detailed below.

Recruitment into the BiBBS cohort is currently undertaken by a team of multilingual Community Research Assistants. The BiBBS community research assistants will offer the referral to IY-T for BiBBS participants. This team has Standard Operating Procedures (SOPs) for contacting and enrolling parents into the intervention. Enrolment of participants onto the IY-T programme will be the responsibility of the project co-ordinator for the IY-T delivery team based at Barnardos, using their usual recruitment procedures.

### Data collection and management

The project-level data regarding the number of women who enrol, participate, and complete the programme will be linked to information on BiBBS participants and used in this feasibility TwiCS.

As per the BiBBS protocol, record matches for routine data linkage will be validated on the basis of NHS number plus multiple non-unique identifiers (e.g. surname, date of birth) where possible. The central database, hosted by BTHFT, will store data obtained from Medway and SystmOne routine health and education data. Data from each source will be linked at the BiBBS person level and will be structured and maintained by BiBBS data managers as a long-term strategic store to service cohort data capture and analysis. The entire database schema and data will be backed up nightly. Further details of the routine data management process can be found in the BiBBS protocol.

### Monitoring

#### Harms

There is unlikely to be harm to individuals from taking part in the intervention as it is non-invasive, though is possible that discussions relating to family relationships could highlight potential safeguarding issues for participating parents and/or their children. To mitigate this risk, the practitioners delivering the intervention and community research assistants making the phone calls are trained in safeguarding. The BiBBS study protocol has been approved by the Bradford and Leeds Research Ethics Committee (15/YH/0455). All BiBBS researchers follow Bradford Teaching Hospital Foundation Trust’s Safeguarding Adults and Safeguarding Children policies.

#### Data monitoring and auditing

This study evaluates an intervention that is already being commissioned by BSB and implemented independently from this study and the evaluation team. The Innovation Hub is conducting regular monitoring of the intervention including reporting on progression criteria that have been agreed with the intervention and Better Start Bradford teams. This information is used by Better Start and the intervention team to inform commissioning and implementation decisions. There are also a number of project management groups for BiBBS conducted within BTHFT described in Additional file 1 in the BiBBS protocol [16]. The sponsor of BiBBS is the BTHFT Research Management and Support Office which may conduct independent auditing of the study.

#### Dissemination policy

Findings will be produced in reports and shared among relevant BSB partners and commissioners in Bradford and England. A briefing will be shared with BiBBS participants through existing communication strategies (including website, social media, newsletters, and birthday cards. Summaries of findings may also be widely reported in the local BSB communities using BiBBS and BSB newsletters, social media, and local press. In addition, the findings from this study will be submitted for publication in scientific journals and as conference abstracts.

## Discussion

Parenting programmes delivered in the early years have the potential to reduce the onset of child mental health difficulties [1, 2]. It is therefore crucial that we find efficient, implementable methods to establish the effectiveness of such programmes. A TwiCS design would overcome many of the limitations of the traditional RCT design and has the advantage of a staged consent process and access to long-term routine data to use as outcomes [9, 10].

The BiBBS cohort presents a unique opportunity to test the feasibility of a TwiCS within an ethnically diverse and deprived community. Given the difficulties of recruiting more disadvantaged populations to trials [23], this feasibility study will give useful information about whether a TwiCS is feasible with such populations. If it is found to be feasible, a larger TwiCS with a sample sufficiently large enough to enable precise estimation of intervention effectiveness could be designed and implemented. A future TwiCS would have the advantage of using routinely linked healthcare and educational data as an outcome, such as the Ages and Stages Questionnaire (ASQ) collected during mandatory 2–2 ½ year health visitor visits [34], or the Early Years Foundation Stage Profile (EYFSP) reported by teachers at the end of a child’s reception year [35]. A fully powered TwiCS evaluation of the IY-T parenting programme would have the potential to improve the evidence base of parenting programmes for parents of children under 3 years old [2, 4, 6].

Overall, the findings from this feasibility TwiCS will be useful for future studies that wish to apply a TwiCS design to ascertain the effectiveness of interventions delivered in the early years, both within and beyond the BiBBS cohort.

## Data Availability

These data cannot be shared publicly as they are available through a system of managed open access. Researchers are encouraged to make use of the BiBBS data, which are available through a system of managed open access. Before you contact us, please make sure you have read our Guidance for Collaborators. Our BiB Executive reviews proposals monthly and we will endeavour to respond to your request as soon as possible. You can find out about the different datasets in our Data Dictionary. If you are unsure if we have the data that you need, please contact a member of the BiB team ([contact]). Once you have formulated your request please complete the ‘Expression of Interest’ form available here and send to [contact]. If your request is approved, we will ask you to sign a Data Sharing Contract and a Data Sharing Agreement, and if your request involves biological samples, we will ask you to complete a material transfer agreement.

## Abbreviations

BiBBS: Born in Bradford’s Better Start
IY-T: Incredible Years Toddler
TwiCS: Trial within a Cohort Study
RCT: Randomised control trial
BSB: Better Start Bradford
